## Abstract

**Background:**

Glaucoma patients with irreversible visual field loss often experience decreased quality of life, impaired mobility, and mental health challenges. Perceptual learning (PL) and transcranial electrical stimulation (tES) have emerged as promising interventions for vision rehabilitation, showing potential in restoring residual visual functions. The Glaucoma Rehabilitation using ElectricAI Transcranial stimulation (GREAT) project aims to investigate whether combining PL and tES is more effective than using either method alone in maximizing the visual function of glaucoma patients. Additionally, the study will assess the impact of these interventions on brain neural activity, blood biomarkers, mobility, mental health, quality of life, and fear of falling.

**Methods:**

The study employs a three-arm, double-blind, randomized, superiority-controlled design. Participants are randomly allocated in a 1:1:1 ratio to one of three groups receiving: (1) real PL and real tES, (2) real PL and sham tES, and (3) placebo PL and sham tES. Each participant undergoes 10 sessions per block (~ 1 h each), with a total of three blocks. Assessments are conducted at six time points: baseline, interim 1, interim 2, post-intervention, 1-month post-intervention, and 2-month post-intervention. The primary outcome is the mean deviation of the 24-2 visual field measured by the Humphrey visual field analyzer. Secondary outcomes include detection rate in the suprathreshold visual field, balance and gait functions, and electrophysiological and biological responses. This study also investigates changes in neurotransmitter metabolism, biomarkers, self-perceived quality of life, and psychological status before and after the intervention.

**Discussion:**

The GREAT project is the first study to assess the effectiveness of PL and tES in the rehabilitation of glaucoma. Our findings will offer comprehensive assessments of the impact of these treatments on a wide range of brain and vision-related metrics including visual field, neural activity, biomarkers, mobility, mental health, fear of falling, and quality of life.

**Trial registration:**

ClinicalTrials.gov NCT05874258. Registered on May 15, 2023.

**Supplementary Information:**

The online version contains supplementary material available at 10.1186/s13063-024-08314-3.

## Administrative information

Note: the numbers in curly brackets in this protocol refer to the SPIRIT checklist item numbers. The order of the items has been modified to group similar items (see http://www.equator-network.org/reporting-guidelines/spirit-2013-statement-defining-standard-protocol-items-for-clinical-trials/).

## Introduction

### Background and rationale {6a}

Glaucoma, an optic neuropathy that results in visual field loss [1], has a profound impact on an individual’s quality of life (QoL) [2], mental health [3], and mobility [4]. In Hong Kong, glaucoma accounted for 10% of visual impairment cases [5]. Various pharmaceutical treatments are available to reduce intraocular pressure and slow the progression of glaucoma [6]. However, the damage to vision caused by glaucoma is irreversible, profoundly affecting daily life. Vision rehabilitation can complement medical treatments by helping glaucoma patients maximize the use of their remaining vision, thereby preserving or recovering functional vision. Certain visual rehabilitation strategies, including the use of optical devices, accessible technologies, and techniques to maximize vision (eccentric viewing), have proven beneficial for reading, mobility, and QoL [7–9]. However, the effectiveness and adoption of these approaches are often hindered by factors like low public acceptance and deterioration of visual functions [10]. Besides, issues related to device usability or psychological factors such as frustration when using the devices can increase the abandonment rate of rehabilitation devices [11]. Hence, there is a growing interest in exploring new approaches to vision rehabilitation that focus on retraining the brain to enhance the neural processing of residual visual information from the retina.

Given that vision loss does not typically result in complete blindness, there is potential for improving residual visual function through reactivating damaged but surviving retinal cells and enhancing the processing of information from healthy cells, a concept known as neuroplasticity [12]. Neuroplasticity provides an optimized view of rehabilitation. While the mechanisms of neuroplasticity in vision science are not fully understood, two principles might be involved [13]: (1) residual visual activation [12] and (2) modulation of the brain’s functional connectivity networks [14]. Emerging evidence has demonstrated that vision can be improved by harnessing neuroplasticity [15–17]. The most commonly employed approaches for leveraging neuroplasticity are perceptual learning (PL) [18, 19] and transcranial electrical stimulation (tES) [20, 21].

PL refers to improved performance of a visual task with repeated practice or training [22, 23]. PL can enhance performance across a wide range of visual tasks including vernier acuity, contrast sensitivity, and motion direction discrimination [22, 24, 25]. The mechanisms underlying PL include altered tuning of neural populations and a gradual reweighting of inputs to perceptual decision-making networks [26]. The application of PL to glaucoma patients is still at an early stage, although initial clinical trial results have been reported. For example, Sabel and Gudlin [27] observed that 3 months of daily training (6 days per week for 1 h per day) significantly improved detection accuracy and reaction time measured using high-resolution perimetry (HRP) compared to a placebo. However, the absence of interim assessments throughout the long duration of intensive training has obscured the dose-response relationship. The confirmation of a dose-response relationship would provide stronger evidence supporting the practical application of PL in glaucoma rehabilitation.

tES is a non-invasive brain stimulation technique that can modify the excitability and synchronization of targeted neural regions and networks. The stimulation is achieved by delivering a mild electric current through electrodes mounted on the head that alters ongoing brain activity [28]. There is a growing body of evidence suggesting that tES could be a useful tool for vision rehabilitation [29, 30]. For example, tES has been found to improve vision in a wide range of clinical conditions, including age-related macular degeneration [31, 32], retinitis pigmentosa [33], amblyopia [20, 34], and hemianopia [35, 36]. Furthermore, results from our phase 1 study in the GREAT (Glaucoma Rehabilitation using ElectricAI Transcranial stimulation—NCT04846140) revealed that a single session of anodal transcranial direct current stimulation (tDCS) enhanced perceptual and electrophysiological measures of vision in patients with glaucoma [37]. Besides, tES is a non-invasive technique that is generally safe and typically associated with only mild, transient discomfort [38, 39]. Therefore, the potential application of tES as a tool for vision rehabilitation in glaucoma patients is promising.

### Objectives {7}

#### Specific objectives

The aims of this study are to (1) compare the effects of monotherapy (either PL or tES) and combined therapy (PL + tES) on improving visual field function; (2) examine whether the interventions influence brain neural activity, and concentrations of neurotransmitters in the brain and blood; (3) investigate the degree to which enhancements in visual field or brain neural activity, brought about by the interventions, act as moderating factors in the improvement of mobility performance, mental health, fear of falling, and QoL; and (4) optimize the training protocol and the optimal dosage for achieving maximal intervention effect in glaucoma patients.

Hypotheses:The combination of PL and tES will result in greater visual field improvements than monotherapy.The intervention effect will increase with longer training duration.The improvement in the visual field induced by the interventions will be accompanied by changes in brain activities and blood biomarkers.An improved visual field will contribute to better balance function, gait performance, and QoL. It will also decrease fear of falling and symptoms of depression or anxiety in glaucoma patients.

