## Interventions

### Explanation for the choice of comparators {6b}

Although both PL and tES have shown beneficial effects in restoring visual functions in patients with glaucoma, it is still unclear whether a combined approach can offer greater benefits than monotherapy. Therefore, our goal is to compare the effectiveness of combined PL and tES with monotherapy in improving the visual field in glaucoma patients. Through this comparative study, we aim to understand the potential combined effects and identify the optimal approach for enhancing visual rehabilitation in glaucoma patients.

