## Discussion

The progressive and irreversible nature of visual impairment caused by glaucoma has a significant profound impact on QoL and poses a serious public health concern. Consequently, there is an urgent need for novel rehabilitation methods that can enhance functional vision and improve the overall well-being of glaucoma patients.

The GREAT study aims to investigate the individual and combined effects of tES and PL on visual field, functional performances, brain activity, and various patient-reported outcomes in glaucoma patients. Importantly, this study examines the dose-response relationship and follow-up of any treatment effects, providing insights into the optimal dosage and duration of these interventions. Furthermore, the study monitors changes in brain activity (as measured by EEG), the neurotransmitter metabolites (as measured by MRS), and biomarkers (as measured by serum analysis) following the intervention. This comprehensive approach aids in understanding the underlying mechanisms and neurophysiological changes associated with the interventions, moving beyond the traditional focus on visual functions such as visual acuity and visual field. Additionally, the study assesses the impact of the intervention on real-world activities through gait and balance tests, as well as questionnaires evaluating mental health, QoL, and fear of falling. This holistic assessment is crucial, as the ultimate goal of vision rehabilitation is to improve functional independence and overall well-being for glaucoma patients.

While the study design is robust, there are several limitations that warrant acknowledgment. The repetitive assessments may induce learning effects across all measured outcomes, potentially limiting the ability to differentiate between true treatment effects and the effects of repeated testing. In addition, the long-term nature of the training sessions poses challenges for both participants and research staff, with fatigue and potential drop-out rates being realistic concerns in this large-scale clinical trial. Despite these limitations, it is important to recognize that if the treatment’s effectiveness is evident in the results, it could yield significant long-term benefits for glaucoma patients. Successful outcomes from this study could pave the way for the integration of tES and PL into standard vision rehabilitation protocols, potentially improving the QoL and functional independence for individuals affected by glaucoma.

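### The abstract aim and objective 1 claim a comparison with tES alone, but no randomized arm receives real tES without real PL

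*Protocol article*

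**What the plan says.** The aim appears in five places in the protocol article, with differing precision.

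- Abstract, Background: the project will "investigate whether combining PL and tES is more effective than using either method alone in maximizing the visual function of glaucoma patients".
- Objectives {7}, objective 1: "compare the effects of monotherapy (either PL or tES) and combined therapy (PL + tES) on improving visual field function". The parenthesis names both single treatments.
- Objectives {7}, hypothesis 1: "The combination of PL and tES will result in greater visual field improvements than monotherapy". No single treatment is named.
- Explanation for the choice of comparators {6b}: "our goal is to compare the effectiveness of combined PL and tES with monotherapy in improving the visual field in glaucoma patients". Again none is named.
- Discussion: "The GREAT study aims to investigate the individual and combined effects of tES and PL on visual field".

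The arms are listed in the abstract's Methods as ("1) real PL and real tES, (2) real PL and sham tES, and (3) placebo PL and sham tES") and repeated in Intervention description {11a}. Trial design {8} confirms three arms at 1:1:1. Statistical methods {20a} specifies a linear mixed model for 24-2 MD, dummy-coded with placebo PL + sham tES as the reference. Section {20b} states that no additional analyses are planned.

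**The concern.** Two single treatments are named as comparators for the combination, and only one of them, PL, has an arm. Suppose the combined arm beats PL + sham tES. That result is compatible with tES alone doing as well as the combination, or better. The abstract's question would remain open although the trial had met its own expectation.

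The protocol does not treat tES alone as an idle alternative. Its Background reports that a single session of anodal tDCS improved perceptual and electrophysiological measures in glaucoma in the phase 1 study, and {6b} starts from the position that both treatments have shown benefit. Section {20a} takes the group with the largest MD gain as having the strongest rehabilitation effect. That ranking leaves out a treatment which objective 1 names. At stake is what the trial may conclude on its primary outcome, not whether its randomized comparisons are valid.

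**Working it through.** **Inputs.** Arms: abstract Methods and {11a}. Allocation: {8}. Model and reference level: {20a}. Sample size: {14}.

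**The plan's own figure.** The protocol attaches no number to this comparison. The only related figure is the total of 144. Using the noncentral F test for multiple regression with f² = 0.1, alpha 0.05 and 80% power, three tested predictors require 114 participants. Then 114 / 0.8 = 142.5, rounded up to 143, or 144 as the next multiple of 3. The number of predictors is not stated; three is an assumption (two gives 100 and then 125; four gives 125 and then 157). Nothing below depends on it.

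**Step 1. Cell means.** Let P = 1 for real PL and T = 1 for real tES. Write

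mean(P, T) = b0 + bP·P + bT·T + bPT·P·T.

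| Cell | P | T | Mean | Randomized? |
|---|---|---|---|---|
| Real PL + real tES | 1 | 1 | b0 + bP + bT + bPT | yes |
| Real PL + sham tES | 1 | 0 | b0 + bP | yes |
| Placebo PL + sham tES | 0 | 0 | b0 | yes |
| Placebo PL + real tES | 0 | 1 | b0 + bT | no |

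**Step 2. Rank.** The three randomized rows are (1,1,1,1), (1,1,0,0) and (1,0,0,0). The matrix has rank 3 for four parameters. With the fourth row (1,0,1,0) the rank would be 4.

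**Step 3. Which contrasts the arms support.** A contrast is estimable only if it is a linear combination of the randomized rows.

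| Contrast | In parameters | Estimable with three arms? |
|---|---|---|
| PL + sham tES vs placebo PL + sham tES | bP | yes |
| Combined vs PL + sham tES | bT + bPT | yes |
| Combined vs placebo PL + sham tES | bP + bT + bPT | yes |
| tES alone vs placebo PL + sham tES | bT | no |
| Combined vs tES alone | bP + bPT | no |
| PL × tES interaction | bPT | no |

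The first and third rows are direct coefficients under the dummy coding in {20a}. The second is the difference between those two coefficients.

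**Step 4. Why the data cannot decide.** Let D be the observed difference between the combined arm and PL + sham tES, so that bT + bPT = D. For any value c, setting bPT = c and bT = D − c reproduces all three arm means exactly. The combination's advantage over tES alone is then bP + c. It is zero when c = −bP and negative when c < −bP. Sample size does not enter, so the 144 / 3 = 48 expected per arm gives no information on it, and neither would any larger number.

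**Step 5. The one way round.** Reading D as the effect of tES alone requires bPT = 0. These arms cannot test that assumption.

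**The case against.** The best defence has four parts.

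*Monotherapy may simply mean PL + sham tES, which is an arm.* This stands for hypothesis 1 and {6b}. Neither names tES alone, and each is consistent with the design on that reading. They need a definition. A reader might infer that they contradict the arms in their own right, but their wording does not go that far; the difficulty reaches them only through objective 1. The defence fails for objective 1 and the abstract, where the comparator is expressly either treatment.

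*Synergy is never promised.* This also stands. A reader might infer from talk of combined effects that the trial undertakes to estimate a PL × tES interaction. No section says so. That the interaction is not estimable follows from the missing cell; it is not a broken promise.

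*The arms are stated plainly and the statistics make no tES-alone claim.* True: {20a} compares the three groups and {14} powers a difference among them, so no planned estimate, significance level or sample size is wrong on this account. But the abstract's aim and objective 1 define what the results will be said to answer, and both go beyond what those estimates can show.

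*This is an article, and a fuller plan may settle the matter.* No analysis plan can supply outcomes for a group that was not randomized. The arms are listed in the text twice, so the missing flow chart does not matter either.

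**Conclusion.** The abstract aim and objective 1 are wrong as written, and the Discussion's individual effects are unsupported for tES as a consequence. Of the two comparisons of the combination with a monotherapy, one (versus PL + sham tES) is a sound randomized contrast and the other (versus tES alone) has no information at any sample size.

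The conclusion rests only on the arm list, taken at face value. It does not rest on the sample-size reproduction or on any assumed effect size. That placebo PL still places 20% of its training positions in the region of interest ({11a}) affects how the reference arm is described, but does not alter which contrasts exist.

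A reader might infer that the design itself is defective or that a fourth arm is required. The documents do not support this. A three-arm add-on design is legitimate and answers three useful questions; the fault lies in the stated claims.

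**What to change.** Keep the three arms and the total of 144, and amend the wording:

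1. **Abstract aim and objective 1:** restate as three contrasts on 24-2 MD: (a) real PL + real tES versus real PL + sham tES, described as the effect of adding tES to PL; (b) real PL + sham tES versus placebo PL + sham tES; (c) real PL + real tES versus placebo PL + sham tES. Contrast (c) should be kept, since the planned model estimates it directly.
2. **Hypothesis 1 and {6b}:** define monotherapy as real PL + sham tES.
3. **Abstract and Discussion:** remove the reference to either method alone and the claim to an individual tES effect.
4. **One added sentence:** tES monotherapy, and hence any PL × tES interaction, is not evaluated in this trial.

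The cost is narrower claims and a protocol amendment. Under section {25}, that means discussion and approval by the steering committee and communication to the ethics committee, with a request for approval if necessary. Recruitment is expected to run to December 2026 and all analysis comes at the end ({21b}), so the change can be made before data lock.

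The alternative, a placebo PL + real tES arm at the same expected size, would bring the total to 4 × 48 = 192. That figure only preserves the arm size and is not a power calculation. The narrower aims do not need it.

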### Trial design {8}

This protocol is designed for a three-arm, double-blind, randomized, superiority-controlled design with 1:1:1 allocation. Figure 1 shows the flow chart of this study.

**Fig. 1 Fig1:**
[figure not shown]
Flow chart for the study

## Methods: participants, interventions, and outcomes

### Study setting {9}

The research study is conducted at two locations in Hong Kong SAR—The Hong Kong Polytechnic University and Grantham Hospital. The Hong Kong Polytechnic University serves as the primary site for all detailed assessments, both before and after the intervention. The university’s well-equipped laboratories and facilities ensure precise and comprehensive data collection, providing a robust foundation for the research. To enhance accessibility and convenience for participants, the training sessions are held at either The Hong Kong Polytechnic University or Grantham Hospital, depending on which location is more suitable for each individual. Grantham Hospital is a public general hospital located in a different area of Hong Kong, allowing the study to reach a broader range of participants across different districts.

### Eligibility criteria {10}

All participants who give their consent undergo a phone eligibility screening. During the screening, they are asked about their medical history, medication history, current eye disease conditions, and overall health status. Those who are potentially eligible are then screened for ocular health, cognitive function, and physical function based on the following inclusion and exclusion criteria.

#### Inclusion criteria

Age from 18 to 80 yearsDiagnosis of primary open-angle or normal-tension glaucoma with relative scotoma in both eyesStable vision for at least 3 monthsAbsence of ocular diseases other than glaucomaHumphrey visual field analyzer (HFA) visual field loss (mean deviation of ≤ − 6 dB) within the central 24° of the visual field for both eyesBest-corrected distance visual acuity (BCVA) of 6/12 (equivalent to 0.3 logMAR) or better for binocular vision and the eye with better visual fieldA cognitive functional score of 22 or above in the Montreal Cognitive Assessment—Hong Kong version (HK-MoCA) [40]

#### Exclusion criteria

Ocular diseases other than glaucoma (e.g., age-related macular degeneration, diabetic retinopathy, moderate to severe cataract) or severe hearing impairment (to ensure that participants can hear the instructions clearly during assessments and training)Severe medical problems (e.g., stroke, Parkinson’s disease) or self-reported neurological (e.g., brain surgery, brain tumor, peripheral neuropathy), or cognitive disorders (e.g., diagnosed dementia or cognitive impairment)Self-reported vestibular or cerebellar dysfunction, history of vertigoUse of medications for neurological or psychiatric conditions that might interfere with motor controlContraindications for tES, including:History of adverse reaction to tESHistory of seizure (epilepsy) in self or a first-degree relativeHistory of frequent or severe headachesHistory of head injury, intracranial surgeryPericranial or intracranial metallic objects (e.g., shrapnel, surgical clips, screws, or wires)History of any neurological disorder (e.g., encephalitis, meningitis, stroke, brain tumor)Advanced, unstable, or uncontrolled medical condition (e.g., recent myocardial infarction, pneumonia, end-stage renal or hepatic failure, poorly controlled diabetes)Pregnancy; sexually active and not using a reliable method of birth controlUse of illicit drugsSignificant alcohol intake (> 2 standard drinks) or sleep deprivation (much less the usual) in the last 24 hAny skin disorder affecting the head or face

### Who will take informed consent? {26a}

This study adheres to the latest version of the Declaration of Helsinki. A trained research assistant obtains informed consent from the participants by providing detailed explanation of the project when they complete the consent form. Informed consent must be obtained before any examinations or questionnaires administered.

